## Abstract

**Introduction:**

Accurate and timely dispatch of emergency medical services (EMS) is vital due to limited resources and patients’ risk of mortality and morbidity increasing with time. Currently, most UK emergency operations centres (EOCs) rely on audio calls and accurate descriptions of the incident and patients’ injuries from lay 999 callers. If dispatchers in the EOCs could see the scene via live video streaming from the caller’s smartphone, this may enhance their decision making and enable quicker and more accurate dispatch of EMS. The main aim of this feasibility randomised controlled trial (RCT) is to assess the feasibility of conducting a definitive RCT to assess the clinical and cost effectiveness of using live streaming to improve targeting of EMS.

**Methods and analysis:**

The SEE-IT Trial is a feasibility RCT with a nested process evaluation. The study also has two observational substudies: (1) in an EOC that routinely uses live streaming to assess the acceptability and feasibility of live streaming in a diverse inner-city population and (2) in an EOC that does not currently use live streaming to act as a comparator site regarding the psychological well-being of EOC staff using versus not using live streaming.

**Ethics and dissemination:**

The study was approved by the Health Research Authority on 23 March 2022 (ref: 21/LO/0912), which included NHS Confidentiality Advisory Group approval received on 22 March 2022 (ref: 22/CAG/0003). This manuscript refers to V.0.8 of the protocol (7 November 2022). The trial is registered with the ISRCTN (ISRCTN11449333). The first participant was recruited on 18 June 2022.

The main output of this feasibility trial will be the knowledge gained to help inform the development of a large multicentre RCT to evaluate the clinical and cost effectiveness of the use of live streaming to aid EMS dispatch for trauma incidents.

**Trial registration number:**

ISRCTN11449333.

Strengths and limitations of this studyThe mixed methods approach to evaluation of feasibility and acceptability uses a combination of routinely collected data, observational data, interviews and survey methods.A comprehensive process evaluation will be undertaken to understand acceptability and impact of using live streaming from the perspective of 999 callers and emergency operations staff.The design (testing for a week each month over 6 months) builds consideration of seasonal variation in trauma into the design, while enabling time to adapt and improve the protocol as the SEE-IT Trial progresses.Recruitment of 999 callers may prove challenging due to the nature of their involvement in incidents; and investigating any impact of wider diversity factors is dependent on the characteristics of callers during the trial periods and we may not have sufficient data for this. The Ambulance Trust where live streaming will be tested uses NHS Pathways (as used in half of Ambulance Trusts in the UK); the SEE-IT Trial will give us insight into how live streaming would work with this dispatch system but may not extrapolate fully to areas that use other systems for triage/decision support.

## Introduction

### Background and rationale

Emergency medical services (EMS) provide emergency medical care at the scene of incidents before patients are conveyed to hospital (eg, blood transfusions and emergency anaesthesia). To save lives and prevent long-term disability, timely and accurate dispatch of pre-hospital resources is critical.^1^ Evidence suggests trauma patients should receive definitive care within 1 hour of the incident (The ‘Golden Hour’), otherwise the risk of morbidity and mortality increases significantly.^2^ Where severe injury is suspected by EMS (eg, major trauma), specialist paramedics in critical care and/or helicopter EMS (HEMS) may be dispatched to the scene to care for the patient and/or convey the patient to hospital.

When a 999 call is made in the UK, the dispatchers in the emergency operations centre (EOC) need to decide which resources to send to the scene by gathering information about what has happened and the clinical state of the patient(s). The dispatchers rely on 999 callers and other bystanders to accurately relay essential information.^3^ However, lay public 999 callers can sometimes provide inaccurate information due to language barriers, subjectivity, the emotional impact of being at the scene and limited medical training or knowledge.^3 4^ Dispatch response is often recognised as a weak link in the EMS chain,^5^ often involving either under-resourcing or over-resourcing.^6–9^ Previous studies have shown that up to 50% of HEMS (air ambulance) dispatch and 25% of road ambulance dispatch for suspected trauma patients are not appropriate.^6–9^

It is vital that EMS are being dispatched to incidents where they are needed due to finite and often limited resources. If dispatchers were able to see the patient and scene via live video streaming through a 999 callers’ smartphone camera, it could be easier to make more accurate and timely decisions about dispatch of EMS.^4^ There is evidence that video-assisted cardiopulmonary resuscitation (CPR) has the potential to improve patient outcomes,^10–16^ but there is a lack of research evidence to support the use of live video streaming for EMS dispatch for trauma.

NHS policies and the Department of Health and Social Care actively encourage the use of innovative technologies to improve patient and healthcare outcomes.^17^ The benefits of using video in other healthcare settings are growing, for example, for remote healthcare consultations,^18–21^ but evidence is sparse in relation to use in pre-hospital settings, despite being used routinely in some ambulance services. There is some limited evidence of the benefits and acceptability of live streaming to aid HEMS dispatch,^4^ but its impact on clinical or economic outcomes has not yet been evaluated. Also, the psychological impact of dispatchers viewing the scene and impact on 999 callers has not been investigated for exposure to trauma.

### Objectives and research questions

Main research question: is it feasible to conduct a future randomised controlled trial (RCT) to assess the clinical and cost effectiveness of using GoodSAM live video streaming to improve targeting of emergency medical resources? The overall aim of this research is to assess the feasibility of implementing and evaluating GoodSAM live streaming in a definitive RCT.

The objectives are:

To obtain data required to inform the design of a subsequent RCT (eg, event rate, screening rate, effect size/precision for outcomes health economic data).To test trial processes including randomisation and data collection methods.To conduct a nested process evaluation to test the acceptability and feasibility of using GoodSAM live streaming from provider and public perspectives (eg, training, video feasibility, video acceptability, psychological harm to 999 callers and/or dispatch staff).

Further research questions relating to these objectives can be found in the study protocol published on the National Institute for Health and Care Research (NIHR) study webpage.^22^

## Methods and analysis

### Trial design and study setting

The SEE-IT Trial is a feasibility RCT with a nested process evaluation in an EOC in South East England (South East Coast Ambulance Service NHS Trust). This study includes two observational substudies (1) in an EOC that routinely uses live streaming to assess acceptability and feasibility of use of live streaming in a diverse inner-city population (London Ambulance Service NHS Trust) and (2) in an EOC that does not currently use live streaming to act as a comparator site regarding the psychological well-being of EOC staff using versus not using live streaming (East of England Ambulance Service NHS Trust). In addition, 11 NHS hospital trusts covered by the main trial site will be involved in identifying and consenting patients for access to their medical records including: University Hospital Southampton NHS Foundation Trust; St George’s University Hospitals NHS Foundation Trust; Medway NHS Foundation Trust; Surrey and Sussex Healthcare NHS Trust; Maidstone and Tunbridge Wells NHS Trust; East Sussex Healthcare NHS Trust; East Kent Hospitals University NHS Foundation Trust; Dartford and Gravesham NHS Trust; King’s College University Hospital NHS Trust; Royal Surrey County Hospital NHS Foundation Trust and University Hospitals Sussex NHS Foundation Trust.

The study was planned to run for 18 months from 1 October 2021 to 31 March 2023. Pressures on the NHS and ambulance services meant the start of the trial period was delayed 4 months to June 2022. Therefore, the overall study end date is now 31 July 2023. There were nine amendments made to the protocol during the feasibility study, outlined in the protocol on the NIHR study webpage.^22^

### Eligibility criteria

This study includes three types of participants; trauma patients, lay public 999 callers and EOC staff. See tables 1 and 2 for inclusion and exclusion criteria, respectively.

**Table 1 T1:** Participant inclusion criteria

Participant type	Main feasibility trial	Inner-city observational substudy	Staff well-being substudy
Trauma patients	All trauma patients during the six trial observation weeks who are the subject of 999 calls involving major trauma, judged by the HEMS dispatcher and/or critical care paramedics (CCPs) as likely to require enhanced dispatch.	All trauma patients during observed shifts that involve trauma and are screened by HEMS dispatchers or critical care advanced paramedic practitioner dispatchers (APPs) who attempt to use GoodSAM during the call.	N/A
Lay public 999 callers	999 callers during the six trial weeks where the incident involves major trauma (defined as per above).	All 999 callers during observed shifts that involve trauma and are screened by HEMS dispatchers or critical care APPs who attempt to use GoodSAM during the call.	N/A
EOC staff	All CCPs, HEMS dispatchers and research paramedics.	All HEMS dispatchers and critical care APPs.	All CCPs and HEMS dispatchers.

CCPs in the main feasibility trial site and APPs in the inner-city observational substudy are the ways different Ambulance Trusts describe specialist paramedics in critical care.

EOC, emergency operations centre; HEMS, Helicopter emergency medical services.

**Table 2 T2:** Participant exclusion criteria

Participant type	Main feasibility trial	Inner-city observational substudy	Staff well-being substudy
Trauma patients	Any emergencies of a suspected medical origin (eg, heart attack or stroke).	Any emergencies of a suspected medical origin (eg, heart attack or stroke).	N/A
Lay public 999 callers	Calls will be excluded where: (1) 999 caller is not at the scene; (2) 999 call originates from a landline; (3) 999 call originates from another emergency service, for example, police or fire; (4) 999 calls where resource (excluding community first responder, CFR) will arrive on scene before live streaming could be activated; (5) 999 call ended before transfer for activation of live streaming; (6) 999 calls where another incident takes priority and (7) calls where clinical acuity is found to be lower than the threshold for the study (not major trauma). All callers identified by the dispatchers as a child caller (under 16 years old) and those who select they are under 16 on the 999-caller survey will be excluded.	All callers identified by the dispatchers as a child caller (under 16 years old) and those who select they are under 16 on the 999-caller survey will be excluded.	N/A
EOC staff	EOC staff not mentioned in the inclusion criteria.	EOC staff not mentioned in the inclusion criteria.	EOC staff not mentioned in the inclusion criteria.

EOC, emergency operations centre.

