### Recruitment: identification and consent

#### Trauma patients

Trauma patients will be identified by research paramedics (RPs), using the eligibility criteria. RPs will observe all trial shifts. For eligible calls in the main trial site, the computer-aided dispatch (CAD) number(s) relating to the incident will be recorded by the RP as the identifier to share with the conveying hospital to approach for consent. Informed consent will be sought from either the patient, their consultee or the patient’s parent or guardian (either in the hospital before discharge or via telephone, email or post) in all hospital trusts included in the trial (trauma units and major trauma centres covered by the EOC). RPs may consent patients in person with assistance from the hospital to identify the patient(s). Approval has been granted by the Confidentiality Advisory Group (Section 251 application) to access medical records for casualties who die before consent can be sought (and where there is not a power of attorney in place for that individual). National data opt-out status will be checked for all deceased patients.

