#### 999 callers

In the main feasibility site, the RP will determine eligibility of the 999 callers and prompt the dispatchers to send a text message via the CAD, inviting the 999 caller to participate in a survey about their experience of calling 999 for the incident. The text message will include a link to the participant information sheet (PIS), consent form and contact details for the research team. A reminder text message will be sent to 999 callers within 1 week of the incident. Those who participate in the survey will be invited to partake in an interview and selected to represent a range in demographics (age, ethnicity, gender), type of incident they witnessed and evidence or not of psychological harm from survey responses.

In the inner-city observational substudy, at the end of the call (once resources have been dispatched) 999 callers will be asked for permission to store their name and number to share with the researcher to be invited to participate in the study. Those who consent will initially be contacted by phone so the researcher can explain the study and ask their permission to send them further details about the study via text message or email. The researcher will then send a text message or email with a link to the PIS and consent form, which once completed will re-direct to the survey. Reminder texts/emails will be sent up to 1 week after the incident. Only those who participate in the survey will be invited to partake in an interview.

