### Assignment of intervention

Working shifts are randomised 1:1 to intervention (GoodSAM) or standard ambulance care using a minimisation algorithm to ensure balance between weekday/weekend (Mon–Thurs vs Fri–Sun) and daytime/night-time shifts (06:00 to 18:00 vs 18:00 to 06:00).

A small number of shifts in the final observation week will be used to test the feasibility of individual call randomisation using a pre-prepared randomisation list. All randomisations will be undertaken by a statistician at Surrey Clincial Trials Unit to ensure the allocation is independent of the research team.

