### Statistical methods and data analysis

#### Quantitative analysis

A full statistical analysis plan (SAP) will be reviewed by key members of the research team and approved by the steering committee before analysis is undertaken.

As this is a feasibility study, statistical analysis will focus on providing estimates and confidence intervals of key rates such as the number of eligible calls per day, uptake of video intervention and timing and appropriateness of dispatch to inform a subsequent RCT. Outcome measure will be summarised by arm and estimates reported with confidence intervals to inform future sample size calculations.

The SAP will outline any expected exploratory analysis of outcomes that may be useful to inform a subsequent RCT including any signal of potential efficacy, but it is noted that the study is not powered for this and so any interpretation would be limited to the direction and magnitude of any effect. Missing data (including outcome data) will be summarised, but all observed data will be included in any analysis according to the randomised allocation following the intention-to-treat principle.

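### Caller exclusions (4) and (5) are applied after the shift's arm is known and rest on live-streaming steps that control shifts do not have; (7) has no fixed time point

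*Protocol article*

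**What the plan says.** All references are to the protocol article.

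- **Allocation.** Under Assignment of intervention, "Working shifts are randomised 1:1 to intervention (GoodSAM) or standard ambulance care using a minimisation algorithm". There is one exception: "A small number of shifts in the final observation week will be used to test the feasibility of individual call randomisation".
- **Who decides eligibility.** Under Recruitment, "RPs will observe all trial shifts", and in the main trial site "the RP will determine eligibility of the 999 callers". No blinding is described. Table 1 defines major trauma as incidents "judged by the HEMS dispatcher and/or critical care paramedics (CCPs) as likely to require enhanced dispatch".
- **Exclusions.** In Table 2, lay-caller row, main trial column, exclusion (4) turns on whether a crew will reach the scene before streaming would have been possible. Exclusion (5) is "999 call ended before transfer for activation of live streaming". Exclusion (7) is "calls where clinical acuity is found to be lower than the threshold for the study (not major trauma". The trauma-patient row excludes only emergencies of suspected medical origin.
- **Pathways.** Under Intervention and randomisation, control calls are voice only. Intervention calls follow the standard pathway until dispatch priority is set. They are then transferred to the HEMS dispatcher or critical care paramedic for streaming, after which resources may be changed.
- **Progression (Table 3).** Row 1 is the share of smartphone callers willing and able to activate streaming (green from 70%, red below 50%). Row 2 is the share of activation requests that lead to viewed footage. Row 3 concerns HEMS stand-down and changed dispatch decisions.
- **Analysis.** Under Quantitative analysis, "all observed data will be included in any analysis according to the randomised allocation following the intention-to-treat principle".

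**The concern.** Randomising shifts balances the calls that arrive in each arm. It does not protect against choosing among those calls once the arm is known. Here the choice is made by staff who know the arm, and two of the rules are written in terms of the intervention. Exclusion (5) has no counterpart in a control shift, because no transfer for streaming takes place there. Exclusion (4) can be applied in a control shift only by imagining when streaming would have started.

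Exclusion (7) raises a different question. It does not say when acuity is to be judged, or from what information. The staff who judge acuity are the staff who receive the video in intervention shifts.

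Two things are at stake:

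- **Comparability of the arms.** The caller survey is affected most directly, because survey invitations follow the eligibility decision. The dispatch outcomes are affected if the caller exclusions carry over to them.
- **The row 1 uptake figure.** It is part of the primary outcome, the progression decision. Removing calls that ended before transfer, or where a crew arrived first, removes calls that did not stream.

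**Working it through.** **1. The article's own precision figures.** Inputs from Sample size and from Intervention and randomisation: 250 incidents, 125 of them intervention, over 42 days.

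- Rate: 250/42 = 5.95 per day. 95% half-width: 1.96 × √250 / 42 = 0.738, which agrees with the stated ±0.75.
- Largest standard error of a proportion on 125: √(0.25/125) = 4.47%, which agrees with the stated figure of under 5%, if the outcome is treated as a proportion.

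These figures reproduce, but they say nothing about selection. The article gives no exclusion rates, so what follows is a sensitivity range.

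**2. Can each rule work alike in both arms?**

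| Exclusion | Intervention shift | Control shift |
|---|---|---|
| (4) | Judged against a real activation step | Hypothetical: no activation step |
| (5) | Observable | No transfer for streaming to precede |
| (7) | Time point open; footage may be available | Time point open; voice information only |

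For (4) and (5) the difference is in the wording. For (7) it is possible but not stated.

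**3. Row 1 uptake under (4) and (5).** Let u be the observed uptake and f the share of otherwise eligible intervention calls removed. Assume all removed calls are non-activations by callers who would otherwise count. Uptake per eligible call is then u × (1 − f). With u = 70%:

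| f (assumed) | Uptake per eligible call | Row 1 band |
|---|---|---|
| 5% | 0.70 × 0.95 = 66.5% | amber |
| 10% | 0.70 × 0.90 = 63% | amber |
| 20% | 0.70 × 0.80 = 56% | amber |
| 30% | 0.70 × 0.70 = 49% | red |

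The 50% limit is reached at f = 1 − 0.50/0.70 = 28.6%. In counts, at f = 20%, 100 of 125 calls are retained, 70 of them activate, and 70/125 = 56%.

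**4. Row 1 uptake under (7).** Assume 65% uptake before exclusion and 10% of calls removed.

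- None of the removed calls had streamed: 0.65/0.90 = 72.2%.
- 65% of them had: (0.65 − 0.065)/0.90 = 65.0%.
- All of them had: (0.65 − 0.10)/0.90 = 61.1%.

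If footage is what reveals low acuity, the last case applies and reported uptake falls.

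**5. Row 3 stand-down under (7).** Assume no true effect, the same stand-down rate s in both arms, and a share x of intervention calls removed, all of which would have been stood down. The observed intervention rate is (s − x)/(1 − x).

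- With s = 50% and x = 10%: 0.40/0.90 = 44.4%, an apparent fall of 5.6 points or 11% in relative terms.
- A spurious 10% relative fall needs x = 0.1s/(1 − 0.9s): 0.05/0.55 = 9.1% at s = 50%, and 0.025/0.775 = 3.2% at s = 25%.
- A spurious 10-point fall needs x = 0.1/(1 − s + 0.1): 0.1/0.6 = 16.7% at s = 50%, and 0.1/0.85 = 11.8% at s = 25%.

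The values of s and x are assumptions. Both readings of the 10% threshold are shown because Table 3 does not say which is meant.

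**The case against.** Much can be said for the plan, and part of it stands.

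- **Exclusion (7) does not mention streaming.** It restates the Table 1 threshold in negative form. The intervention text and row 3 treat a change of dispatch after footage as an outcome, which argues against using footage to exclude calls. A reader might infer that (7) is tied to the intervention and inflates uptake. The article supports neither: the link is only a possibility left open by the missing time point, and step 4 shows that footage-driven exclusion would lower uptake.
- **Row 2 is little affected by (5).** It counts activation requests, and a call that ended before transfer would normally have produced none. A reader might extend the denominator problem to both uptake rows; for (5) it belongs to row 1.
- **Uptake among callers who reach the activation step is a legitimate feasibility measure.** This stands, and is why both denominators are wanted.
- **The exclusions sit in the caller row.** A reader might conclude that stand-down, speed and appropriateness are certainly compared on differently selected calls. That is plausible, since the row speaks of calls being excluded and the Trauma patients section records incident numbers for hospital consent for eligible calls. It is not certain, because the patient row lists only medical emergencies.
- **Context.** Efficacy signals are exploratory, qualitative data also inform progression, and the individually randomised final-week shifts may differ.

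None of this makes (4) and (5) workable alike in both arms, or brings dropped calls back into an analysis by allocation.

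**Conclusion.** The point holds for (4) and (5) on the wording alone. For shift-randomised calls they are applied after allocation, by staff who know the arm, and refer to steps absent from control shifts. The arms can therefore be selected differently, and the commitment to analyse by allocation covers only the calls that remain.

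For (7) the defect is the missing time point and information source. Contamination by footage is an inference, and its risk is to row 3.

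The size of any bias cannot be computed from the article. On assumed removals of 5% to 30%, an observed row 1 uptake of 70% corresponds to between 66.5% and 49% of otherwise eligible calls, so the band could move from green to amber or red. The stand-down figures likewise show how little removal would be needed under the stated assumptions; they are not estimates of what happened.

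**What to change.** For shift-randomised calls:

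1. Define the analysis set identically in both arms, from information in the computer-aided dispatch log up to the point where dispatch prioritisation is determined, before any transfer or footage. Make the acuity check in (7) at that same point.
2. Keep calls that meet (4) or (5), or are later found to be of lower acuity, in the by-allocation comparison of routinely recorded dispatch outcomes. Code these as recorded reasons for non-activation and report their counts by arm.
3. Report row 1 uptake both per eligible call and per caller reaching the activation step, and state which denominator drives the progression decision.
4. State whether the caller-row exclusions also apply to patient-level outcomes.

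The change is mainly one of wording plus a time-stamp rule. Its costs are lower reported uptake, a more diluted effect, and possibly some additional consent approaches and survey texts, because both follow from the eligibility decision.
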